### Participant selection and screening

Participants will be excluded if they meet any of the following criteria:•Self-reported diagnosed mental health disorders•Self-reported hearing impairments•Inability to tolerate wearable sensing devices or experimental procedures•Evidence of acute or chronic sleep deprivation, defined as insufficient sleep duration or extreme baseline sleepiness, identified during pre-session screening as described below.

To characterize sleep status and identify potential sleep deprivation prior to laboratory testing, a multi-tiered sleep assessment will be conducted. Wearable-based sleep monitoring will be conducted prior to the laboratory session. Participants who already use consumer smartwatches (e.g., Apple Watch, Fitbit, or Google Pixel Watch) will report their sleep timing data (bedtime and wake time) for the 3 nights preceding the application to participate in the study. For participants without a smartwatch, a Fitbit device will be provided to collect sleep timing and duration data for a minimum of 3 consecutive nights. Consumer-grade wearables have demonstrated reasonable accuracy, particularly for estimating total sleep duration, when compared with medical-grade devices [28,29]. In addition to wearable-based sleep tracking, baseline subjective sleepiness will be assessed before each laboratory session using the Karolinska Sleepiness Scale (KSS).

Participants meeting any of these criteria will be excluded to avoid potential confounding effects of acute or chronic sleep deprivation:•Average sleep duration is <5 h across monitored nights as measured by a smartwatch•Baseline KSS score ≥ 7

Sleep assessment will be conducted at the time of application, and only eligible participants will be notified and will subsequently be invited for pre-experiment assessment (see next section).

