#### Pre-session sleep quality and baseline sleepiness assessment

At the beginning of the session, participants will be greeted and their readiness to proceed will be confirmed. Sleep quality from the previous night, as measured by a smartwatch, will be reviewed. Baseline sleepiness will be assessed using the KSS. These data will be used to verify that the participant does not meet the exclusion criteria. Participants will then be instructed to observe the stimuli naturally without performing any explicit task. They will also be informed that they are free to yawn (or not) according to their natural inclination throughout the session, including during baseline recording.

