After the first condition, a standardized wakefulness reset period of approximately 15 min will be implemented. During this period, laboratory lighting will be increased, and participants will be encouraged to engage in light activities such as standing, brief walking, or casual movement. These activities are intended to promote wakefulness without inducing excessive physical exertion. Intentional or exaggerated upper-body stretching will not be encouraged, in order to minimize potential facilitation of yawning behaviour. Light conversation may be used when necessary to reduce accumulated sleep pressure. At the end of the reset period, subjective sleepiness will again be assessed using the KSS to confirm that participants have returned to an adequate level of alertness. If participants continue to exhibit signs of drowsiness, the reset period may be extended, or additional light activities may be introduced before proceeding.

The second condition will then follow the same procedure as described above. Upon the completion of both conditions (with and without sound), all physiological sensing equipment will be removed.

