### Data collection and management

#### Data collection overview

Physiological data will be collected continuously during the experimental sessions using a multimodal sensing setup. Questionnaire data will be collected at multiple timepoints. Table 1 summarizes all data that will be collected and their corresponding instruments.

**Table 1 tbl0001:** Data collection summary.

Instruments	Data collected	Data collection timing
Consumer-grade smartwatches	Sleep duration, sleep schedule	Participants screening, and throughout the experiment days
KSS questionnaire	Baseline and post-condition subjective sleepiness levels	Participants screening, pre-experiment session baseline, post-condition, end of wakefulness reset period
MCTQ questionnaire	Chronotype	Pre-experiment assessment
PSQI questionnaire	Subjective sleep quality over the past one month	Pre-experiment assessment
Big Five Personality	Personality traits	Pre-experiment assessment
Research-grade smart wristband	Blood volume pulse (BVP), heart rate variability (HRV), electrodermal activity (EDA), 3-axis acceleration, and skin temperature	Experimental sessions
Eye-tracking system	Pupil diameter of both eyes	Experimental sessions
Functional near-infrared spectroscopy (fNIRS) system	Changes in HbO_2_ and HHb in the prefrontal cortical regions, head movements captured by 3-axis acceleration	Experimental sessions
Video recorder	Used solely to identify observable yawning behavior (counts of yawning, eye closure duration); recordings will be permanently deleted after feature extraction	Experimental sessions
Simple Likert Scales	Stimulus naturalness and comfort ratings	Experimental sessions
Semi-structured interview	Post-experiment interview responses	Post-experimental assessment

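### A single KSS rating of 7 or more at the start of session 2 excludes a participant who has already been randomised and has completed session 1, where moving that session would keep the human–digital pair

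*Protocol article*

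**What the plan says.** Under Participant selection and screening, the article gives two sleep-related criteria: average monitored sleep below 5 h, and "Baseline KSS score ≥ 7". The consequence is stated for the person: "Participants meeting any of these criteria will be excluded to avoid potential confounding effects of acute or chronic sleep deprivation".

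On timing, the same section says three things:

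- Sleep deprivation is "identified during pre-session screening as described below".
- For the KSS, "baseline subjective sleepiness will be assessed before each laboratory session using the Karolinska Sleepiness Scale (KSS").
- It closes with "Sleep assessment will be conducted at the time of application, and only eligible participants will be notified".

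The section on pre-session sleep quality and baseline sleepiness then has the KSS taken when the participant arrives, and says "These data will be used to verify that the participant does not meet the exclusion criteria". Table 1 gives the KSS timing as "Participants screening, pre-experiment session baseline, post-condition, end of wakefulness reset period".

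Phase 2 gives both sessions the same structure, assigns one stimulus type to each, randomises their order, and sets a minimum interval of one day with no maximum. The second session is booked at the end of the first. No section provides for moving a session, or says what becomes of session 1 data after an exclusion at session 2.

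**The concern.** The KSS records how sleepy someone is at that moment. The article treats it that way: it repeats the rating within a session and separates the two sessions partly because sleepiness passes. A person-level exclusion suits a lasting characteristic, and one afternoon rating of 7 is not necessarily that. The average sleep duration criterion addresses lasting sleep loss directly.

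The timing makes this costly. A failure at application is ordinary ineligibility. A failure at session 2 comes after the order has been assigned and one stimulus type has been seen. Human versus digital is compared only across sessions. It is research question 2 and a planned comparison in the primary analysis (Table 2). A participant removed at that point has no second half of the pair. Removal also depends on sleepiness, the construct that the primary outcome measures, so these losses need not be random.

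**Working it through.** **Does the text fix this consequence?** Set side by side:

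1. The criterion is a KSS of 7 or more, and participants who meet it are excluded (Participant selection and screening).
2. The KSS is taken before each laboratory session (same section).
3. The session-start data are used to check the exclusion criteria (pre-session assessment section).
4. Both sessions follow the same structure, so the check recurs at session 2 (Phase 2).
5. Each session carries one stimulus type (Phase 2).

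From 1 to 4, a rating of 7 or more at session 2 leads to exclusion of the participant. From 5, the lost within-person information is human versus digital and its interaction with sound. Sound versus no sound is compared inside each session, so session 1 still informs it if the data are retained.

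**Does anything prevent moving the session?** No. Only a minimum interval is set.

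**Size.** The article states no sample size, dropout rate or rate of KSS ≥ 7, so there is no figure to reproduce. Let *p* be the probability that someone who completed session 1 rates 7 or more at the start of session 2. The values of *p* are assumptions.

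- Pairs lost at session 2 as written: *p*
- Pairs lost if the session may be moved once, days independent: *p* × *p*
- Enrolment for 100 complete pairs: 100 / (1 − loss), rounded up
- Standard error of a purely paired human–digital contrast, relative to no loss: 1 / √(1 − loss)

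| Assumed *p* | Loss as written | Loss with one move | Enrolment for 100 pairs, as written / one move | Relative SE, as written / one move |
|---|---|---|---|---|
| 5% | 5% | 0.05² = 0.25% | 106 / 101 | 1.026 / 1.001 |
| 10% | 10% | 0.10² = 1% | 112 / 102 | 1.054 / 1.005 |
| 15% | 15% | 0.15² = 2.25% | 118 / 103 | 1.085 / 1.011 |

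For example, at 10%: 100 / 0.90 = 111.1, so 112; and 1 / √0.90 = 1.054.

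The first loss column is simply the assumption restated; the information lies in the comparison with the second. If the same people tend to be sleepy on every visit, a move rescues fewer of them than *p* × *p* implies.

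**The case against.** The best defence is that no sentence describes a participant being removed at session 2. The pre-session section says the criteria are checked, not what follows, and what staff do after a failed check is the kind of detail an article leaves to the full protocol. This stands in part: the fuller document may hold a rebooking rule. But the article is not silent on the consequence. It says that participants who meet the criterion are excluded, and it applies the criterion at each session. If exclusion was meant only at application, the pre-session section contradicts that.

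Several stronger readings are tempting, and the documents do not support them.

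- **Larger losses.** A reader might count every check. At 5% to 15% each, 1 − (1 − *p*)² gives 10% to 28% over two sessions, and 1 − (1 − *p*)³ gives 14% to 39% with application included. Those totals rest on assumed rates and independence, and mostly count people who fail before seeing any stimulus. They do not measure the harm described here.
- **A broken crossover.** The planned mixed model can use incomplete participants, and the sound contrast survives. The check precedes that day's stimulus, and nothing suggests that losses would differ by session order beyond chance.
- **Harm to the moderator analyses.** A reader might infer that the rule narrows the range for research question 4 and that rebooking restores it. Under rebooking every session still starts below 7, so the range of baseline sleepiness is unchanged. Nothing in the article ties a momentary rating to chronotype or habitual sleep quality.
- **Unequal handling of drowsiness.** After the reset the rule is milder: "If participants continue to exhibit signs of drowsiness, the reset period may be extended, or additional light activities may be introduced before proceeding". But that drowsiness comes at least 5 + 5 + 10 + 15 = 35 minutes of recording, stimulus, assessment and reset after set-up, may be produced by the session, and has no KSS threshold attached. The contrast shows that delay is an accepted response to drowsiness; it does not prove an inconsistency.
- **Dropping the KSS at application.** That would be a preference about eligibility, not a correction.

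**Conclusion.** The point holds as a matter of what the article states: the person-level KSS exclusion is re-applied at session 2, and its literal consequence is the loss of a randomised participant's human–digital pair. This is a rule set at the wrong level, not a gap.

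Its size cannot be established from the documents. Under an assumed 5% to 15% failing at session 2, 5% to 15% of pairs are lost as written and 0.25% to 2.25% with one permitted move, with independence between days. The standard error of a purely paired contrast would rise by about 3% to 8%, against 0.1% to 1.1%. The mixed model recovers some between-person information if session 1 data are kept, so those increases are upper figures for the assumed rates. The article does not say whether the data are kept. The point deserves a change because the remedy is small and protects a planned primary comparison.

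**What to change.** Leave the threshold and the screening criteria as they are. Reconcile the screening section with the pre-session section so that:

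1. a failed KSS check at the start of a session applies to that session, which is not run and is rebooked on another day in the same time slot, with the assigned session order kept;
2. the number of attempts is limited to a figure set in advance;
3. session 1 data from anyone who still cannot complete session 2 remain in the mixed model.

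This takes a few sentences and breaks no stated rule, since only a minimum interval is given. The downside is some repeat visits and a longer interval between sessions for a few participants.

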#### Equipment and environment setup

The physiological sensing setup will begin with positioning the wrist-worn device. Prior to placement, the wristband battery will be confirmed to be fully charged. The device will be fitted on the participant’s non-dominant wrist and adjusted to achieve a snug yet comfortable fit that prevents sliding during the session.

Next, the eye-tracking system will be configured. Participants will be seated at a fixed distance of approximately 60–70 cm from a display screen while wearing the eye-tracking device, which is mounted on the participant’s head and positioned in front of the eyes. The fit and placement of the eye tracker will be adjusted to ensure comfort and optimal alignment with the participant’s eyes. A calibration sequence will then be performed in accordance with the manufacturer’s instructions [34]. Pupil detection quality will be checked immediately after calibration, and the experiment will proceed only after satisfactory tracking performance is confirmed.

The fNIRS system will then be configured. A Brite system (Artinis Medical Systems, The Netherlands) will be used, which operates at dual wavelengths (760 nm and 850 nm) with a sampling rate of 50 Hz. A cap with 27 channels (10 transimitters and 8 receivers; source-detector 3 cm apart) will be positioned on the participant’s head to cover bilateral prefrontal cortical regions. Optodes will be placed according to the international 10–20 system, with channels centered over positions approximately corresponding to the FpZ-F3-Cz-F4-FpZ regions. Prior to data collection, optode-scalp contact quality will be verified for each channel using the system’s built-in signal quality indicators [35]. Channels with consistently low signal quality indices will be flagged and excluded from analysis on a per-participant basis. In cases where contact quality is suboptimal, a shower cap will be fitted over the fNIRS cap to reduce ambient light interference and improve optode-scalp coupling. Data collection will proceed only after satisfactory signal quality is confirmed across a minimum of 20 channels. Raw optical signals will be converted to changes in oxygenated (HbO₂) and deoxygenated (HHb) hemoglobin concentration using the modified Beer-Lambert law as implemented in the NME-NIRS Python package [36].

Finally, a video camera will be positioned to capture the participant’s facial expressions throughout the session. The camera angle will be adjusted to ensure a clear view of the face, and ambient lighting will be optimized to support subsequent behavioral coding. A brief test recording will be conducted to confirm that facial features are clearly visible.

To ensure consistency across participants, the experimental environment will be standardized. Room temperature will be maintained between 20 and 22 °C throughout the session. Lighting conditions will be controlled at a moderate and consistent level. External noise and potential interruptions will be minimized as much as possible. Participants will be seated comfortably in a chair with back support, and the display screen will be positioned at eye level and at an appropriate viewing distance to reduce physical strain.

Following equipment setup, a five-minute baseline physiological recording will be conducted. This duration was selected based on prior studies examining the signal lengths required to reliably derive downstream physiological and cognitive indices [[37], [38], [39]]. Participants will be instructed to sit quietly in a reclining chair and relax while maintaining their gaze on a neutral fixation point displayed on the screen. All physiological signals will be recorded continuously during this period. To avoid introducing confounding influences, no conversation or additional instructions will be provided during the baseline recording.

#### Experimental procedure

Each experimental session includes two yawning stimulus conditions (with sound and without sound) presented in randomized, counterbalanced order. To minimize social presence effects on yawning responses [40,23], participants will remain alone in the experimental room throughout stimulus presentation, while the experimenter monitors the session remotely from an adjacent space via a live physiological data feed and video stream.

At the beginning of each condition, physiological recording will begin continuously, and participants will be instructed to watch the videos naturally and to maintain a comfortable and relaxed posture. No further instructions regarding yawning will be given at this stage, as participants will have been informed of their freedom to respond naturally at the pre-session assessment stage.

Stimulus presentation will then proceed for approximately 5 min. Each stimulus sequence will consist of approximately 50 discrete yawning events, each approximately 6 s in duration [41,42]. This duration is consistent with prior experimental yawning paradigms in contagious yawning research and falls within the commonly used 3–5 min exposure range [15,22]. During this period, all physiological signals will continue to be recorded continuously, and participant behavior will be monitored via the video recording. Particular attention will be given to signs of sleep onset such as sustained eye closure. If sleep onset occurs, the corresponding timestamp will be noted, and recording will continue without interruption.

Following stimulus presentation, a post-condition assessment period of approximately 10 min will be conducted. Video will be stopped, and subjective sleepiness will be assessed using the KSS. Participants will also complete a brief questionnaire regarding their yawning behavior, including whether they yawned or experienced an urge to yawn [40].

After the first condition, a standardized wakefulness reset period of approximately 15 min will be implemented. During this period, laboratory lighting will be increased, and participants will be encouraged to engage in light activities such as standing, brief walking, or casual movement. These activities are intended to promote wakefulness without inducing excessive physical exertion. Intentional or exaggerated upper-body stretching will not be encouraged, in order to minimize potential facilitation of yawning behaviour. Light conversation may be used when necessary to reduce accumulated sleep pressure. At the end of the reset period, subjective sleepiness will again be assessed using the KSS to confirm that participants have returned to an adequate level of alertness. If participants continue to exhibit signs of drowsiness, the reset period may be extended, or additional light activities may be introduced before proceeding.

The second condition will then follow the same procedure as described above. Upon the completion of both conditions (with and without sound), all physiological sensing equipment will be removed.

##### Post session questionnaires

At the end of the experimental session, participants will complete post-session questionnaires assessing the perceived comfort and naturalness of the yawning stimuli and provide open-ended feedback. If the completed session is the first session, the second session will be scheduled at this time.

### Phase 3: post-experimental assessment and debriefing

After completion of both experimental sessions, participants will take part in a final semi-structured interview to reflect on their overall experience, including perceived effects of the stimulus and any discomfort or fatigue experienced during the study.

Following the interview, a debriefing session will be conducted. During this session, the full purpose of the study (including the use of yawning stimuli) will be explained. Participants will be informed that the specific focus on yawning was not disclosed prior to the experiment in order to minimize expectation effects and demand characteristics. Participants will be given the opportunity to ask questions about the procedures or the potential findings. They will also be provided with the opportunity to withdraw data if desired.

### Yawning stimulus materials

Human yawning stimuli will be compiled from publicly available video recordings, drawing on sources such as YouTube (the “yawn-o-meter”), TikTok, and the YawnStim dataset [43]. Clips will be selected based on clear visibility of facial expressions and the presence of naturalistic yawning behavior. Each condition will include approximately 50 discrete, non-repeating yawning events, each lasting 6 s [41,42], resulting in a total stimulus duration of 5 min. The final stimulus set will include a balanced representation of male and female individuals.

Digital character yawning stimuli will be generated using generative AI tools to produce controlled yet diverse animated yawning clips. Stylized animal-like characters (e.g., cats and dogs) will be used to reduce potential confounds associated with human identity, attractiveness, or familiarity, while preserving clearly recognizable yawning behavior. Animal-like characters were selected because they are sufficiently human-dissimilar to avoid uncanny valley effects, yet sufficiently familiar to elicit socially contagious responses, consistent with prior evidence that contagious yawning occurs across species [44]. Each clip will be structured to reflect the typical temporal phases of a yawn, including gradual mouth opening, peak extension, and closure, with smooth motion transitions. Slight variations in timing and motion will be introduced to maintain naturalness while avoiding repetition. All generated clips will undergo manual selection and standardization to ensure experimental consistency. Clips with ambiguous expressions, unnatural motion, or technical artifacts will be excluded. Remaining clips will be standardized in duration, resolution, and presentation format.

For audiovisual conditions, yawning sounds will be synchronized with the peak mouth-opening phase of each clip, while silent conditions will use identical clips without audio. For the human yawning clips with audio, the original audio from the source clips will be retained. For digital pet clips and human yawning clips without audio, yawning sounds will be synthesized using audio generation tools. Generated sounds will be standardized in amplitude and duration and evaluated for perceived naturalness prior to use. Stimulus sequences will be matched across human and digital pet conditions in terms of the number of yawns, inter-yawn intervals, and total duration.

All candidate clips (both human and digital pet) will be independently evaluated by two trained research assistants who are blind to the study hypotheses. Each clip will be assessed based on the clarity of yawning behavior, absence of ambiguity with other facial actions, and technical quality. Only clips with unanimous agreement across all criteria will be included. Inter-rater agreement will be quantified using Cohen’s *K*, and any disagreements will be resolved through adjudication by a third rater.

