#### Data pre-processing

Physiological and behavioral data will be time-aligned across sensing modalities using synchronized timestamps. For each yawning condition, physiological signals will be segmented into predefined analysis windows relative to stimulus onset.

Artifact removal will then be performed separately for each sensing modality. For wristband-based signals, visual inspection and accelerometer data will be used to identify motion artifacts, signal dropout, and periods of excessive movement, which will be excluded from further analysis. For eye-tracking data, periods of sustained eye closure indicative of potential sleep onset as well as poor-quality pupil measurements, will be excluded. For fNIRS data, standard preprocessing procedures including bandpass filtering and motion artifact correction will be applied, followed by the removal of segments affected by low signal quality. Raw optical signals will subsequently be converted into HbO_2_ and HHb concentration changes.

To ensure that analyses capture stimulus-related physiological responses rather than transitions into sleep, only data recorded prior to identified sleep onset will be included in confirmatory analyses. Data segments affected by excessive artifacts, signal loss, or sustained eye closure will be excluded from primary analyses. Baseline correction will be applied to all physiological measures to account for inter-individual differences in resting physiological states. Baseline values will be calculated for each participant using pre-stimulus periods and subtracted from condition-specific values or expressed as percentage changes, as appropriate.

Following signal cleaning, physiological features will be extracted for each experimental condition. BVP will be used to compute mean heart rate and HRV metrics, including SDNN, RMSSD, and frequency-domain measures. EDA data will be analyzed to derive tonic skin conductance level and phasic skin conductance responses. Pupil data will be used to calculate mean pupil diameter, pupil diameter variability and pupillary unrest index (PUI). Skin temperature data will be summarized using mean peripheral temperature and changes relative to baseline. For fNIRS data, temporal patterns of cortical oxygenation changes will be extracted. Finally, descriptive statistics will be used to summarize participant characteristics, baseline sleep measures, and data completeness.

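### Soundtrack level is standardised only for generated audio and film luminance is not matched, so the type-by-sound interaction on KSS and the human–digital and change-from-baseline pupil contrasts can reflect stimulus properties

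*Protocol article*

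**What the plan says.** All stimulus rules are in the protocol article under Yawning stimulus materials.

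- **Source of human clips.** "Human yawning stimuli will be compiled from publicly available video recordings", including video-sharing sites and a research dataset.
- **Audio of human clips that have sound.** "For the human yawning clips with audio, the original audio from the source clips will be retained".
- **Audio of all other clips.** "For digital pet clips and human yawning clips without audio, yawning sounds will be synthesized using audio generation tools".
- **Scope of audio standardisation.** "Generated sounds will be standardized in amplitude and duration and evaluated for perceived naturalness prior to use".
- **Matching between types.** "Stimulus sequences will be matched across human and digital pet conditions in terms of the number of yawns, inter-yawn intervals, and total duration".
- **Visual standardisation**, given in the paragraph on digital clips: "Remaining clips will be standardized in duration, resolution, and presentation format".
- **Silent versions.** "silent conditions will use identical clips without audio".

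Elsewhere, Equipment and environment setup controls room lighting and describes a five-minute baseline spent looking at a fixation point. Data pre-processing lists the pupil features: "Pupil data will be used to calculate mean pupil diameter, pupil diameter variability and pupillary unrest index (PUI"). It also subtracts a pre-stimulus baseline or expresses the measures as a percentage change. Table 2 plans three comparisons for the primary outcome, KSS: human versus digital, sound versus silent, and their interaction. It applies the same model to each physiological outcome.

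**The concern.** The audio rule is asymmetric as written. Every digital soundtrack is generated, levelled and checked for naturalness. The human soundtrack mixes generated sound with source audio from varied recordings, for which no levelling or naturalness check is stated. Adding sound can therefore be a stronger or weaker manipulation for humans than for digital characters, simply because of playback level. The interaction is meant to show whether sound works differently with the two kinds of face, and it would absorb that difference.

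The visual rule has a similar gap for one family of secondary outcomes. Pupil size responds directly to light. Collected footage of people, generated animation and a fixation display have no stated reason to share a mean luminance. A human–digital difference in pupil measures, or a change from baseline, could then be read as arousal when it reflects the screen.

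Both differences belong to the films and act in the same direction for every participant. Randomising and counterbalancing order does not remove them, and a larger sample does not shrink them.

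**Working it through.** The article states no sample size, power or effect size, so there is no figure of its own to reproduce. The check is contrast algebra on the four cells, followed by an illustration.

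**Step 1. Nuisance terms per cell.** Let lumH and lumD be the effect of film luminance on the outcome (relevant to the pupil), and loudH and loudD the effect of soundtrack level. Luminance is the same in the sound and silent versions of one type, because the clips are identical.

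| Cell | Nuisance |
|---|---|
| Human, sound | lumH + loudH |
| Human, silent | lumH |
| Digital, sound | lumD + loudD |
| Digital, silent | lumD |

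**Step 2. What remains in each contrast.**

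| Contrast | Luminance left | Loudness left |
|---|---|---|
| Human − digital, averaged over sound | lumH − lumD | 0.5 (loudH − loudD) |
| Human − digital, silent films only | lumH − lumD | 0 |
| Human − digital, sound films only | lumH − lumD | loudH − loudD |
| Sound − silent, averaged over type | 0 | 0.5 (loudH + loudD), part of the intended manipulation |
| Interaction | (lumH − lumH) − (lumD − lumD) = 0 | loudH − loudD |
| Change from baseline, one condition | film luminance − fixation-screen luminance | level of that film's sound, if any |

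**Step 3. Which planned analyses are touched.**

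- KSS interaction: the full loudness difference.
- KSS human–digital main effect: half of it.
- KSS sound–silent main effect: no between-type loudness difference.
- Pupil human–digital contrast: the luminance difference plus half the loudness difference.
- Pupil change from baseline: the luminance step between fixation screen and film.
- Pupil sound–silent contrast: no luminance term. The pupil interaction has none either, if luminance acts additively.

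**Step 4. Illustration for the interaction.** Let b be the loudness bias in SDs of the within-subject interaction contrast and n the number of participants. Both are assumptions. At two-sided 0.05 (Data analysis), by normal approximation, the chance of rejecting a true null is

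Φ(b√n − 1.96) + Φ(−b√n − 1.96).

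For b = 0.2 and n = 20, b√n = 0.894, which gives Φ(−1.066) + Φ(−2.854) ≈ 0.143 + 0.002 = 0.145.

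| b | n = 20 | n = 30 | n = 40 | n = 60 |
|---|---|---|---|---|
| 0 | 0.050 | 0.050 | 0.050 | 0.050 |
| 0.1 | 0.073 | 0.085 | 0.097 | 0.121 |
| 0.2 | 0.145 | 0.195 | 0.244 | 0.341 |
| 0.3 | 0.269 | 0.376 | 0.475 | 0.642 |

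**Step 5. After the fix.** With loudH = loudD the interaction term is 0 and the rate returns to 0.05. With lumH = lumD the luminance term leaves the human–digital pupil contrast. The baseline change is free of it only if the fixation screen is matched as well.

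**The case against.** **Natural versus synthetic sound is part of the question.** A digital character has no original voice, and keeping real human sound is a reasonable choice for naturalism. This stands: requiring one sound-production route for both types would change what is compared. It does not explain why retained audio should escape levelling.

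**Other controls exist.** Two raters, blind to the hypotheses, screen all clips. Events last 6 s, sounds are synchronised to peak mouth opening, and participants rate naturalness and comfort. These help with clip quality and timing. The rating criteria are clarity, lack of ambiguity and technical quality, and none of them equalises sound level or brightness.

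**Screen settings may sit in a fuller document.** This has some force for luminance, where the point rests on a list that leaves it out. The list is explicit, however, and the article offers its standardised human–digital comparison as a value of the protocol. The amplitude rule is stated text.

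**The article disclaims causal effects.** That disclaimer concerns yawning against neutral stimuli. Relative differences between conditions are still claimed, and those are the contrasts affected.

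**Pupil measures are secondary** and are to be read as complementary indicators. This is true, and it limits the consequence of the luminance half.

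**A reader might infer more.** One could conclude that every pupil contrast is confounded by light, that luminance biases the primary interaction, or that all three primary comparisons suffer from unequal audio. The document supports none of these. The clips are identical within a type, so luminance drops out of the sound contrast. No path from luminance to KSS is shown. In the sound–silent main effect, sound level is part of the manipulation itself.

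**Conclusion.** The concern holds in limited form. Following the audio rule as written allows loudness to differ systematically by stimulus type. That difference falls wholly on the planned type-by-sound interaction for KSS and by half on the human–digital main effect. Unmatched luminance allows the human–digital and change-from-baseline pupil contrasts to reflect screen light. The sound-versus-silent pupil contrast is sound on this point, and so is the pupil interaction as regards light, provided luminance acts additively.

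The size of either bias cannot be computed, because the article gives no sound levels, luminances, sample size or outcome variances. It also does not say what share of human clips will keep source audio. The rejection rates above show only how a fixed offset behaves under assumed values. They are not estimates for this study, and the true offset could be close to zero. The point merits a change because it touches a planned primary comparison and cannot be fully repaired once data are collected.

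**What to change.** Before the stimuli are locked:

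1. Put every soundtrack, retained human originals included, through the same amplitude standardisation and the same naturalness check.
2. Match the mean luminance of the human films, the digital films and the fixation screen by video processing, and add luminance to the list of matched attributes.
3. If luminance is not matched, state that pupil results on stimulus type and on change from baseline will not be interpreted as arousal, and rely on the sound-versus-silent contrast for pupil inference.

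A film-mean luminance covariate is not a substitute. Pupil features are extracted per condition, so if all participants see the same films, mean luminance takes one value per stimulus type and is collinear with that factor.

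The cost is one batch-processing step on stimuli that have yet to be compiled and generated, and slightly less natural-looking source clips. The design, the sessions and the primary model stay as they are.
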